### Preparation of Medhya Avaleha

Medhya Rasayana Avaleha is the polyherbal combination of Centella asiatica, Convolvulus prostratus, Tinospora cordifolia, and Glycyrrhiza glabra mentioned in Table 3. Drugs required for the preparation of Medhya Avaleha will be collected from local markets or herbal gardens and identified in the Dravyaguna Department. Preparation of Medhya Rasayana Avaleha will be done as per classical reference [25] in Rasashastra and Bhaishyajya Kalpana Department of MGACHRC, Salod Wardha.

**Table 3 table3:** Overview of contents of Medhya Rasayana Avaleha [26].

Contents	Parts used	Proportion	Maximum dose
Centella asiatica (Linn.); family: Apiaceae; Ayurveda name: Mandukparni	Leaves	1 part	mg/kg [27]
Convolvulus prostratus (chois); family: Convolvulaceae; Ayurveda name: Shankhpushpi	Leaves, roots, barks, flowers,	1 part	mg/kg [28]
Tinospora cordifolia (Willd Miers); family: Menispermaceae; Ayurveda name: Guduchi	Barks	1 part	Extracts 120 mg/kg [29]
Glycyrrhizaglabra (Linn.); family: Fabaceae; Ayurveda name: Yashtimadhu	Roots	1 part	50 gm/day [30]

### Yoga Pose

For yoga poses refer to Figures 2-4.

**Figure 2 figure2:**
[figure not shown]
Yoga pose 1.

**Figure 3 figure3:**
[figure not shown]
Yoga pose 2.

**Figure 4 figure4:**
[figure not shown]
Yoga pose 3.

### Assessment of Participants

All participants will be assessed for level of addiction, social behavior, and Prakruti (physical and mental constitution) before initiating the intervention during the study at 0, 30, 60, and 90 days, and on the follow-up day at180 days at Mahatma Gandhi Ayurved Hospital Salod (H). For the assessment of gadget addiction, an internet addiction test scale [31] questionnaire and a digital addiction scale [32] will be used. There are 20 statements on this questionnaire. After carefully reading each statement, participants have to choose the response (0, 1, 2, 3, 4, or 5) that best describes him or her using the 5-point Likert scale. Select the option that most accurately reflects how participants have been spending their time over the past month if 2 options seem to fit equally well. Along with participants, their parents or caretakers will be asked the following question regarding the gadget-addicted behavior of their children and the mean of both scores will be calculated to avoid bias in the study. The social behavior of the patient will be assessed by *DSM-5* [33] criteria on the proposed day Prakruti examination will conducted on the day of initiation of intervention by Ayusoft software [34].

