**Primary objectives**
To evaluate the efficacy of Medhya Rasayana in gadget addiction with an internet addiction test scale, a digital addiction scale, and *DSM-5* (*Diagnostic and Statistical Manual of Mental Disorders* [Fifth Edition]).To evaluate the efficacy of Ayurveda nonpharmacological interventions in gadget addiction with an Internet addiction test scale, a digital addiction scale, and *DSM-5*.To assess the comparative efficacy of 3 therapeutic modalities in the management of gadget addiction by Internet addiction test scale and *DSM-5*.

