## Methods

### Study Design

A 3-arm superiority randomized controlled trial will be performed. The study flow is depicted in Figure 1. Patients with gadget addiction will be selected from the Kaumarbhritya Outpatient Department of MGACHRC Salod, Wardha as per inclusion criteria mentioned in Textbox 2. During the first visit, Parents will be asked whether they would like to deaddict their child from gadget addiction if they are willing then written informed assent will be obtained from the participants’ guardian. Participants will then complete questionnaires on the internet addiction test scale and digital addiction scale. Furthermore, participants’ social behavior and Prakruti (physical and mental constitution) will be assessed. As well as age, gender, socioeconomic status, and type of gadget he or she is using frequently, and the purpose of gadget use will be assessed. After this period, participants will be randomly allocated to both intervention groups in a 1:1 allocation ratio. After this, Medhya Rasayana will be prescribed to participants in group I according to age-wise doses at a frequency of twice a day for a period of 90 days as mentioned in Table 1. Participants allocated to group II will be counseled regarding the adverse effects of gadget addiction on physical and mental health and advised to follow the following routine daily for a period of 90 days, details of nonpharmacological interventions are described in Tables 1 and 2. Yoga (sun salutations, meditation), Targeted reduction in Gadget use time Padanshik krama, that is, reduce gadget use time by one-fourth part each week. Reduced time will be used for adventure, bravery, cognitive skill-oriented things, sports, and yoga. Patients will be counseled to play indoor and outdoor games daily. Encouragement toward attending social programs whenever required and feasible, encouragement of parent-child relationship by advising parents to spend a minimum of 2 hours of quality time daily with children and to give a reward for not using mobile with encouraging children to learn new things, participate in group activities with peers and teach etiquette. Initial training in sun salutation and the method of meditation will be given to participants and their parents at the time of enrollment. Children will be asked to do the proposed sun salutation and meditation on the assessment day. Participants not responding or not following instructions will be eliminated from the study. Group III will be the external group due to the fact that cognitive behavioral therapy requires trained professionals and there are time and financial constraints as well. Hence, in this published data of previously conducted clinical trials, cognitive behavioral therapy intervention in the management of gadgets or internet addiction will be used for comparison with Medhya Rasayana and Ayurveda nonpharmacological interventions. On the 30th, 60th, and 90th days of treatment, participants will be evaluated using the internet addiction test scale and the *DSM-5* (*Diagnostic and Statistical Manual of Mental Disorders, Fifth Edition*) scale for social behavior. A follow-up will be conducted on the 180th day to determine whether the intervention’s possible effects are lasting.

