
**Figure 1 figure1:**
[figure not shown]
Consolidated Standards of Reporting Trials (CONSORT) flow diagram.

Inclusion and exclusion criteria.Inclusion criteriaParticipants irrespective of gender, religion, and socioeconomic status.Participants affected with gadget addiction as per case definition, that is internet addiction test score: 31-79.Age group between 6-16 years with signs and symptoms of gadget addictions as per *ICD-10* (*International Statistical Classification of Diseases, Tenth Revision*) or 11 as follows.Parents who are willing to provide written informed consent for their children to be included in the study.Exclusion criteriaInternet addiction test score >80.Children aged <6 years and those aged >16 years.Parents who are not willing to provide written informed consent for their children to be included in the study.Children experiencing from behavioral diseases, locomotor diseases, genetic diseases, and systemic disorders.

**Table 1 table1:** Overview of interventions.

	Group P	Group N	Group C
Participants, n	80	80	External group
Name of medication	Medhya Rasayana	Nonpharmacological	Cognitive behavioral therapy
Dosage form	Young’s formula	As per schedule	—^a^
Duration	90 days	90 days	—
Assessment with IAT^b^ scale	0, 30, 60, and 90 days	0, 30, 60, and 90 days	—
Follow up with the IAT scale, digital addiction scale, and *DSM-5*^c^ scale	180th day	180th day	—
Route or mode of administration	Oral	—	—
Anupana	Lukewarm water	—	—

^a^Not applicable.

^b^IAT: internet addiction test.

^c^*DSM-5*: *Diagnostic and Statistical Manual of Mental Disorders* (Fifth Edition).

**Table 2 table2:** Overview of Ayurveda nonpharmacological intervention.

Intervention	Details of method	Duration and frequency
Counseling (Satvavajaya)	Counseling about hazardous effects of mobile and benefits of mobile deaddiction	Fortnight 1 session with parents and child separately
Yoga therapy	Surya Namaskar, Dhyana	Daily
Encouragement for indoor and outdoor games	Patients will be counseled to play indoor and outdoor games daily	Daily for1hour
Encouragement towards attending social programs	Parents will be guided for engagement of children in learning new things, in group activities with peers, etiquette	“Si-opus sit” Whenever required and feasible
Encouragement of parent-child relationship	Parents are advised to spend time with their children. And advised to give a reward for not using mobile to child.	Minimum 2 hours of quality time daily by parents

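### Primary objective 3 sets a child-parent averaged IAT score in groups P and N against published CBT results that cannot be put on that score, so a common measurement is not secured

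*Protocol article*

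**What the plan says.** Three parts of the Protocol article bear on this point.

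- **Primary objectives (Textbox 1).** The third objective is "To assess the comparative efficacy of 3 therapeutic modalities in the management of gadget addiction by Internet addiction test scale" together with DSM-5.
- **Assessment of Participants.** The addiction questionnaire has 20 statements, each answered 0 to 5. A parent or caretaker is questioned about the child as well. The rule for combining the two ratings is that "the mean of both scores will be calculated to avoid bias in the study". A separate sentence deals with DSM-5: "The social behavior of the patient will be assessed by *DSM-5* [33] criteria". It mentions no averaging.
- **Study Design.** Group III (group C) is external. Its data come from "published data of previously conducted clinical trials, cognitive behavioral therapy intervention in the management of gadgets or internet addiction will be used for comparison". Only groups P and N are randomised and assessed.

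The article does not say that a child-only score will be used when P or N is set against group C.

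**The concern.** The averaging rule creates a composite specific to this trial. For P versus N that does no harm to comparability, because both arms are scored alike. For P or N versus group C it does matter: the CBT results are already published under whatever rater their authors chose, and this trial cannot add a parent rating to them.

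The hypothesis section frames the trial as asking whether P or N does better than the control group, and the abstract plans ANOVA and regression across the three groups' interventions. Both presuppose one response variable. If the scores differ in rater, a difference between P or N and the CBT figure mixes treatment effect with a rater offset, and a larger sample does not reduce that offset. The issue is separate from the lack of randomisation: it would remain if the populations were identical.

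The protocol itself gives reason to expect the two raters to differ. It averages them in order to limit bias, and the Discussion expects overdiagnosis driven by overconscious parents. In group N the parents also help deliver the intervention, through daily time with the child and rewards for not using the mobile, so their ratings may move during treatment.

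**Working it through.** **The plan's own figure.** No figure in the plan depends on the averaging rule. The sample size reproduces: (1.64 + 0.84)² × [0.622 × 0.378 + 0.362 × 0.638] / 0.20² = 6.1504 × 0.46607 / 0.04 = 71.66, rounded up to 72, and 72 / 0.9 = 80. It matters here only because it is built on a proportion with internet addiction, which is a cut-off type of outcome.

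**Inputs from the article.** Total range 20 × 5 = 100 points; case definition IAT 31 to 79; score in P and N = mean of child and parent.

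**Inputs assumed (not in the article).** The CBT source used child self-report. The gap is g = parent minus child, taken as 0 to 15 points in either direction. For the spread, child and parent SDs are equal, with correlation r from 0.2 to 0.9.

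**1. Absolute score.** Composite = (child + parent)/2 = child + g/2.

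| g | Offset g/2 | Child score at which the composite reaches 31 (31 − g/2) |
|---|---|---|
| 0 | 0 | 31 |
| 5 | 2.5 | 28.5 |
| 10 | 5 | 26 |
| 15 | 7.5 | 23.5 |

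If parents score below the child, the signs reverse. The last column uses the lower bound of the case definition as an illustrative cut-off; it shows why a proportion above a cut-off is affected even when g is constant.

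**2. Change from baseline.** Change in composite = change in child score + (g at follow-up − g at baseline)/2. With constant g the second term is 0 and the offset cancels. If g falls from 10 to 0 during treatment, the term is (0 − 10)/2 = −5, so the composite shows 5 points more improvement than the child's own score.

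**3. Spread.** SD of composite / SD of child score = √((1 + r)/2). This is 0.775 at r = 0.2, 0.866 at r = 0.5 and 0.975 at r = 0.9. A standardised effect would therefore not be on the same footing as one from a self-report source, even with g = 0.

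**4. Which analyses are exposed.** The article names repeated measures ANOVA and the chi-square test, and gives a reduction in gadget addiction as a primary outcome. Comparing mean change is protected if g is stable. Comparing endpoint means, or proportions classed as addicted, is not.

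**The case against.** The strongest reply is that no CBT source is named, so its instrument and rater are unknown and a mismatch is not demonstrated. That stands: the documents show that sameness is not secured, not that the scores differ.

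Three stronger readings are tempting and should not be made.

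- A reader might take the dashes for group C in Table 1, footnoted as not applicable, as proof that the CBT data lack IAT and DSM-5 scores. The same dash stands under duration and dosage form. It shows only that this trial neither treats nor assesses that group.
- A reader might extend the averaging to DSM-5. The averaging sentence is about gadget-addicted behaviour, and the DSM-5 sentence stands apart from it.
- A reader might conclude that the offset could by itself create or hide superiority. For change from baseline with a stable rater gap it cancels, and with g = 0 there is no mean shift at all.

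It is also fair to say that a condensed article may leave the selection criteria for external data to a fuller document, and that objective 3, by naming the IAT, already implies a limit on the sources. Missing criteria alone would be no finding. But the article itself fixes the scoring rule for P and N and the published source for C, and naming the IAT does not settle who completed it.

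Finally, the lack of randomisation is the larger weakness of group C. That is true, and matching raters does not cure it; it removes one avoidable difference.

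**Conclusion.** The point holds in a limited form. As written, the IAT comparison in primary objective 3 sets a two-rater mean against published scores that cannot be re-rated in the same way, so comparability is not established. On the assumption that the CBT source is child self-report, the shift in absolute scores is 0 to 7.5 points on a 100-point scale for a rater gap of 0 to 15 points. It applies to endpoint means and cut-off proportions. It reaches change from baseline only if the gap moves during treatment. The gap sizes and the rater in the CBT source are assumptions. For DSM-5 the only issue is whether any CBT source reports the same measure. P versus N and the sample size are unaffected. The correction is worth making because it is cheap, not because a mismatch has been proved.

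**What to change.** In Assessment of Participants, state that the child and parent IAT totals are recorded and kept separately, and that their mean is the score for P versus N.

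In objective 3 and the analysis text, state that for any comparison with group C:

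- the IAT total from P and N is the one from the same rater as in the CBT report, normally child self-report;
- it is taken at the visit nearest that report's end of treatment;
- only reports that give IAT totals are used;
- DSM-5 enters the three-way comparison only if a CBT source reports the same measure;
- where no matching report exists, CBT results are described in text, with no formal P-versus-C or N-versus-C comparison.

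The cost is a few lines of wording. No new data are needed, since both totals must exist before they can be averaged. The downside is that fewer CBT reports will qualify. The text should also say that rater matching leaves group C non-randomised.

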### Data Quality Assessment

The researchers will oversee and direct the process of gathering data. Since this study is a component of a postgraduate doctoral degree project, no committee was specifically tasked with overseeing or monitoring the data trials. However, the study progress will be discussed monthly with the supervisor.

#### Statistical Analysis

The data collection phase will be concluded with statistical analysis. Repeated measures ANOVA test, and chi-square test, will be used for statistical interpretation. A statistician consultation will be considered for the selection of the proper statistical method.

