**Methods:**

A randomized, parallel, triple-arm interventional study will be conducted on diagnosed participants of gadget addiction with an age group of 6- to 16-year-old children, which will be selected and equally distributed in 2 groups. Group P will be given Medhya Rasayana (pharmacological intervention), group N will be nonpharmacological Ayurveda intervention, and group C (cognitive behavioral therapy) will be an external group. The Study duration is 180 days with assessment at baseline, midpoint, and endpoint Appropriate statistical techniques, such as ANOVA and regression analysis, will be used to examine the data and evaluate the efficacy of the 3 groups’ interventions. We will perform subgroup analysis according to initial addiction severity, gender, and age. Primary outcome measures include a reduction in gadget addiction and changes in the psychosocial well-being of participants. Standardized questionnaires and instruments will be used to collect data.

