### Participants

The required sample size was calculated by using the following formula.

To evaluate the effectiveness of the therapeutic modalities for managing internet addiction, several key parameters are defined. The type I error rate () is set at 5% and the type II error rate (β) is set at 20%. The true proportion difference, represented by ε, is assumed to be 0. δ denotes the clinically relevant difference at 20% superiority. Initially, the proportion of individuals with internet addiction (P1) is 62.22% (0.622). After the intervention (P2), this proportion decreased to 36.2% (0.362). To determine the appropriate sample size for the study, a clinically accepted difference of 20% is used. The sample size is calculated according to the formula N=(1.64+0.84)2(0.622)(1–0.622) +0.362(1–0.362)/(0.20)2. Based on this formula, the required sample size is 72 individuals per group. To account for a 10% dropout rate, the sample size is increased to 80 per group.

Therefore, 80 participants will be recruited after randomization in each group from the Kaumarbhritya OPD of Mahatma Gandhi Ayurved College Hospital and specialty camps held in peripheral villages of Wardha city. A computer-generated random number table will be used to avoid selection bias in the study. The principal investigator will carry out the process of randomization and enroll the participants. To be eligible for participation, participants should fulfill the inclusion criteria as mentioned in Textbox 2. Patients having any characteristics of exclusion criteria will be excluded from participation in the study.

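### The trial is sized on a proportion addicted that no objective names, while the objectives use scales, the listed tests are tied to no outcome or visit, and the method is left open

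*Protocol article*

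**What the plan says.** All references are to the protocol article.

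- **Sizing (Participants).** The outcome is binary: "the proportion of individuals with internet addiction (P1) is 62.22% (0.622"), falling to 0.362 after intervention. The type I error "is set at 5% and the type II error rate (β) is set at 20"%. Sidedness is not put into words, but the formula uses 1.64. The result is 72 per group, raised to 80 for 10% dropout.
- **Objectives (Textbox 1).** The first two primary objectives judge each Ayurveda intervention on the IAT, a digital addiction scale and DSM-5. The comparative one begins "To assess the comparative efficacy of 3 therapeutic modalities in the management of gadget addiction by Internet addiction test scale" and adds DSM-5. No proportion, cut-off or deciding visit is given.
- **Entry (Textbox 2).** The case definition is an IAT score of 31 to 79, and every enrolled child must meet it.
- **Tests.** The Statistical Analysis section says "Repeated measures ANOVA test, and chi-square test, will be used for statistical interpretation". The abstract says "Appropriate statistical techniques, such as ANOVA and regression analysis, will be used to examine the data".
- **Choice of method.** The Statistical Analysis section adds: "A statistician consultation will be considered for the selection of the proper statistical method". The Results section says the trial started in December 2023.
- **Comparisons.** Study Design randomises 1:1 between the two Ayurveda groups. The cognitive behavioral therapy group is external, taken from published trials. The Hypothesis section nevertheless tests each Ayurveda intervention against control.

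**The concern.** A sample size supports a claim only for the outcome and test it was worked out for. Here the sizing is for a difference in proportions, the objectives are on scales, and the first-named test in the Statistical Analysis section, repeated measures ANOVA, analyses scores. Nothing in the article joins the three.

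Two things are at stake. First, a reader would take 80% power to cover the comparison of IAT scores, and it does not. Second, a score test and a test of a dichotomised score on the same children can disagree. With no deciding analysis named and the method still to be chosen, nothing in the article says which result would count.

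**Working it through.** **1. The plan's own figure.** Inputs from the Participants section: z values 1.64 and 0.84, P1 = 0.622, P2 = 0.362, difference 0.20. The printed expression is read with its squares and bracket restored.

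- Variance term: 0.622 × 0.378 + 0.362 × 0.638 = 0.2351 + 0.2310 = 0.4661
- n = (1.64 + 0.84)² × 0.4661 / 0.20² = 6.1504 × 0.4661 / 0.04 = 71.66, so 72 per group
- Dropout: 72 / (1 − 0.10) = 80 per group

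The figures reproduce, so the arithmetic is not at fault. The value 1.64 is the one-sided 5% point. The same formula at two-sided 5% gives 91.45, so 92. The 72 therefore belongs to a one-sided comparison of two proportions.

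**2. Does that proportion exist in this trial?** P1 is described as the initial proportion addicted. By the trial's own case definition that proportion is 100% at entry, so 62.2% cannot describe the enrolled children unless another cut-off is meant, and none is given. The outcome used for sizing has no defined counterpart among the objectives.

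**3. What the sample supports on a score.** The article gives no SD and no expected mean difference for any scale, so the result can only be in SD units. With 72 completers per arm, the difference detectable with 80% power is (z_α + 0.842) × √(2/72), where √(2/72) = 0.1667:

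- two-sided 5%: (1.960 + 0.842) × 0.1667 = 0.47 SD
- one-sided 5%: (1.645 + 0.842) × 0.1667 = 0.41 SD

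Power at two-sided 5% with 72 per arm, for assumed differences:

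| Assumed difference | Power | n per arm for 80% |
|---|---|---|
| 0.3 SD | 44% | 175 |
| 0.4 SD | 67% | 99 |
| 0.5 SD | 85% | 63 |

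Depending on an SD and a difference that the article does not give, power on the score could lie well below or somewhat above 80%.

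**4. Error rate if two tests could each decide.** For two unadjusted two-sided 5% tests, the chance of at least one false positive under the null is 1 − 0.95² = 9.75% if they are independent. Simulation of correlated test statistics (400,000 draws) gives 9.1% at correlation 0.5 and 7.0% at 0.9. The correlations are assumptions. One named deciding test keeps 5%.

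**The case against.** The strongest reply is that this is an article. Ranking of tests, the primary model and any multiplicity rule may sit in a full protocol or analysis plan that is not shown. That stands as far as mere silence goes. It does not cover what the article itself states: a binary sizing outcome, objectives on scales, two differing lists of tests, and a sentence saying the method is still to be selected. Those statements need reconciling wherever the detail is kept.

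A second reply is that the pieces could be compatible. The objectives name instruments rather than mean scores, and cases are defined by an IAT threshold, so a proportion could be derived. Chi-square could then test it, or could serve the secondary objective on constitution. This also stands in part: the fault is a missing link, not an impossibility.

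Some stronger readings are tempting, but the article does not support them:

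- **That the method will be chosen only after data collection or with results in hand.** The Statistical Analysis section places the analysis at the end of data collection, but gives no date for the consultation. What can be said is that the choice is open in a trial already under way.
- **That the 5% error is broken.** The article is silent on adjustment. It can only be said that protection is not shown.
- **That regression and a group-by-time interaction are rival primary tests, pushing the error well above 10%.** Regression appears only in the abstract, after a phrase marking it as an example, and the interaction is not named at all. Counting them as extra verdicts on the same IAT contrast is a construction.
- **That the inflation is at least one and a half times 5%.** At correlation 0.9 it is 7.0%, or 1.4 times.

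**Conclusion.** The point holds as a mismatch inside the article. The stated 80% power attaches to a one-sided comparison of proportions that no objective names, and which the entry rule makes inapplicable at baseline by the trial's own case definition. It does not carry over to the score analysis. No listed test is tied to a primary outcome or visit, and the method is expressly left open.

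The possible cost in error is moderate: about 7% to 9.75% instead of 5% if two unadjusted tests could each carry the conclusion. That range rests on an assumed correlation of 0.9 to 0, and on neither test being subordinate. The cost in power cannot be fixed, because no SD is given. In SD units the detectable difference is firm: about 0.47 two-sided or 0.41 one-sided with 72 completers per arm.

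**What to change.** 1. **Name one deciding analysis** for the only randomised contrast, group P versus group N. One workable choice is the IAT score at day 90, the end of treatment, compared between groups with adjustment for baseline IAT. Label the proportion addicted (chi-square, with its cut-off and visit stated) and all other tests supportive. Make the abstract and the Statistical Analysis section list the same methods.
2. **Replace the sentence** "A statistician consultation will be considered for the selection of the proper statistical method" with a statement that the method is fixed before outcome data are analysed by group. As the trial has started, date the amendment.
3. **State the sidedness and restate the sizing on the score**, as a detectable difference: with 72 completers per arm, 80% power for about 0.47 SD at two-sided 5%, or 0.41 SD at the one-sided 5% that 1.64 implies. This describes what the existing sample can detect; it does not show that such a difference is expected. Converting it to IAT points needs an SD from outside the article, with its source given.
4. **Reconcile the Hypothesis section**, which compares each intervention with the external control, with a P-versus-N deciding contrast.

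The cost is wording, with no additional children. There are two real consequences. A positive result on the proportion alone becomes supportive only. Step 4 changes which hypothesis decides the trial, so it should be made openly as an amendment.

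### Repeated-measures ANOVA with no baseline adjustment named is a valid but usually inefficient choice for the IAT score; a baseline-adjusted mixed model would use the same data better

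*Protocol article*

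**What the plan says.** The Statistical Analysis section of the protocol article states: "Repeated measures ANOVA test, and chi-square test, will be used for statistical interpretation". It adds: "A statistician consultation will be considered for the selection of the proper statistical method". It gives no factors, covariates, visits or contrast. The abstract's Methods paragraph describes the analysis differently: "Appropriate statistical techniques, such as ANOVA and regression analysis, will be used to examine the data".

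Study Design, Table 1 and Assessment of Participants together put the IAT at days 0, 30, 60 and 90, with follow-up at day 180. Treatment in both randomized groups (P and N) lasts 90 days. Group C is external, so the randomized comparison is P against N.

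**The concern.** Repeated-measures ANOVA is the only method named in the body of the article that suits a score measured repeatedly over time. Three features of its conventional form fit the trial's question poorly.

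- **Group main effect.** It averages over all visits, including day 0, where randomization makes the expected difference zero. A real effect is diluted.
- **Group-by-time F.** It spreads the signal over several degrees of freedom. A significant result says that the profiles differ somewhere, not by how much P and N differ at the end of treatment.
- **Complete visits.** The classical computation uses only children seen at every visit included.

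At stake is power and precision on the randomized comparison, in a trial whose Discussion lists small sample size among its main limitations.

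**Working it through.** **The plan's own figure.** The Participants section uses proportions 0.622 and 0.362, a difference of 0.20, and normal quantiles 1.64 and 0.84.

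- Variance term: 0.622 × 0.378 + 0.362 × 0.638 = 0.2351 + 0.2310 = 0.4661.
- n = (1.64 + 0.84)² × 0.4661 / 0.20² = 6.1504 × 0.4661 / 0.04 = 71.7, so 72 per group.
- With 10% dropout: 72 / 0.9 = 80.

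The figure reproduces. It rests on a proportion, so the model chosen for the IAT mean does not change it.

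**Assumptions for the comparison of methods.** The article gives no IAT standard deviation, correlation or mean effect. Assumed here: a P minus N difference of 0.45 SD at day 90, 72 completers per arm, equal correlation r between visits of 0.3, 0.5 or 0.7, and a two-sided 5% test.

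**Targeted day-90 tests, by formula.** Power ≈ Φ(0.45 × √(72/2) / √f − 1.96) = Φ(2.70/√f − 1.96), where f is the variance relative to a comparison of day-90 scores alone. For a change score f = 2(1 − r); for ANCOVA f = 1 − r².

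| r | f, change | Power, change | f, ANCOVA | Power, ANCOVA |
|---|---|---|---|---|
| 0.3 | 1.40 | 62.6% | 0.91 | 80.8% |
| 0.5 | 1.00 | 77.0% | 0.75 | 87.7% |
| 0.7 | 0.60 | 93.6% | 0.51 | 96.6% |

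**Repeated-measures ANOVA, by simulation** (visits 0, 30, 60 and 90; same assumptions). Simulated ANCOVA power agreed with the formula to within about two points.

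- *Effect building linearly to day 90.* The group-by-time test has about 49% power at r = 0.3, 64% at r = 0.5 and 87% at r = 0.7. Simulated day-90 ANCOVA runs from about 80% to 96% over the same range. The group main effect at r = 0.5 has about 41%.
- *Full effect from day 30.* Group-by-time against day-90 ANCOVA is about 80% vs 87% at r = 0.5 and 96% vs 97% at r = 0.7. The gap is about 17 points at r = 0.3, where the group main effect (about 84%) slightly exceeds day-90 ANCOVA (about 80%).

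**Where the gap comes from (linear onset, r = 0.5, simulated).** The omnibus interaction has 64%, the single day-0-to-day-90 change contrast 77%, and ANCOVA 89%. So 77 − 64 = 13 points come from testing one contrast instead of an omnibus, and 89 − 77 = 12 points from adjusting for baseline instead of subtracting it.

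**Complete-visit analysis.** If each of four follow-up visits is missed independently with probability m, the number kept out of 80 is 80 × (1 − m)⁴:

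- m = 2%: 73.8, about 74
- m = 5%: 65.2, about 65
- m = 10%: 52.5, about 52

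These rates are assumptions. The article states only 10% dropout in total.

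**The case against.** The strongest reply is that this is a preference and not an error. Between randomized arms, repeated-measures ANOVA is a valid test. Contrasts can follow the omnibus F, and the article does not exclude them. Baseline in the outcome vector is not itself a flaw, because a longitudinal model that constrains the baseline means to be equal is about as efficient as ANCOVA. All of that stands. However, conventional repeated-measures ANOVA imposes no such constraint, and the article names neither a contrast nor an adjustment.

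Four stronger readings are tempting, and the documents do not support them:

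- **That the plan fixes an unadjusted analysis as its main test.** No text says so. The abstract also mentions regression, and the final method is left open.
- **That children with a missed visit will be dropped.** This is a property of the classical computation, not a stated rule. A day-90 ANCOVA would likewise lose children without a day-90 score, so baseline adjustment alone does not cure it.
- **That attrition bias follows.** Nothing in the article shows that missed visits would relate to outcome, and the calculations above do not test it. Keeping only 52 of 80 requires a missed-visit rate well above what the stated 10% total dropout suggests.
- **That the method will be chosen with results in view.** The article gives no date for the consultation.

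The gain also depends on unknown inputs. Limiting baseline IAT to 31–79 may lower r and shrink it.

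**Conclusion.** The point holds as a worthwhile improvement to a valid plan. Under the stated assumptions the interaction test gives up roughly 9 to 31 points of power against day-90 ANCOVA when the effect builds linearly (96 − 87 and 80 − 49), and about 1 to 17 points when it is immediate. The advantage is usual but not universal: with an immediate effect it nearly vanishes at r = 0.7, and the group main effect can win narrowly at r = 0.3. In the linear case at r = 0.5, about half the gap comes from targeting one contrast. The direction is well supported. The size rests on an assumed effect, correlation and onset that the article does not supply.

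**What to change.** In Statistical Analysis, replace repeated-measures ANOVA for the IAT by a linear mixed model for the scores at days 30, 60, 90 and 180. Include arm, visit, arm-by-visit, baseline IAT and baseline-by-visit, and use all available visits. Name the P minus N contrast at day 90, the end of treatment, with its 95% confidence interval, as the main estimate. With complete data, and with the covariance between visits left unstructured, this contrast is essentially the day-90 ANCOVA examined above. With missed visits it also keeps children who have at least one follow-up score. Chi-square can stay for supportive comparisons of categories. Bring the abstract's description into line, and settle the wording, with any statistical consultation, before outcome data are examined.

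The cost is a change of analysis wording. No new data, visits or participants are needed, and the 72 and 80 per group stand. The model does not remedy the separate statement in Study Design about eliminating participants, nor the lack of a randomized group C.
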